### Ethical considerations

Both studies have been approved by the Medical Ethical Committee of the Academic Medical Centre Amsterdam, December 2007. Full ethical approval for these studies has been obtained. (CMO number 07.17.1758). All participating centres obtained approval of their local Medical Ethical Committees.

### Economic evaluation

Cost effectiveness is evaluated using the costs per patient without of SUI at 12 months after surgery as the primary outcome measure. In addition, the cost utility is evaluated using the costs per quality adjusted life-year as the primary outcome measure. We aim to evaluate, from a societal perspective, whether concomitant surgery is more cost effective than prolapse surgery alone, with incontinence surgery in second stage if needed. We also want to evaluate whether the use of urodynamic investigation in continent women prior to surgery is more cost effective than non invasive methods to screen for OSUI. Incremental cost-effectiveness analyses will be performed and corresponding cost-effectiveness acceptability curves will be drawn for different values of society's willingness to pay to prevent one extra patient without SUI or to gain an extra quality adjusted life-year. Costs include direct medical costs, non-direct medical costs, and indirect costs of lost days at work and lost productivity while at work.

The needed data on resource use and health status will be gathered prospectively in case record forms and with patient questionnaires, in particularly, the Health and Labour Questionnaire short form and the EQ-5D.

Unit costs will be based on the Dutch 2004 guidelines for costing in health care research and indexed for base year 2008 using yearly general consumer price indices[26].

Quality adjusted life years will be derived from the observed EQ-5D health score profiles at baseline and during follow up by using available time trade-off based health valuation algorithms (and assuming each score profile to represent a patient's health status in-between the actual and the previous measurement [23,24].

### Sample size calculation

#### CUPIDO I trial

Of women with POP and predominant SUI 70% are expected to be cured of their SUI by prolapse surgery. A 20% increase in success rate is expected in concomitant surgery. For each arm 57 women are needed to prove the hypothesis with a power of 80% and one sided testing at 0.05. Taking into account 10% loss to follow up a total of 126 patients will be included in the study. We expect that 30% of the patients with POP will meet the criteria for the study.

#### CUPIDO II trial

For the group of women with occult SUI 73 are needed in each arm to prove a 15% difference in SUI 12 months postoperatively in concomitant surgery and prolapse surgery without midurethral sling (95% versus 80% continence respectively), with a power of 80% and α of 0.05. Taking into account 10% loss to follow up 160 patients will be randomized. We expect 60% of the patients with POP to meet the criteria for the study, and 50% of these patients to have OSUI. We will therefore include 320 women in the study to perform urodynamic investigation.

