**Methods/Design:**

The CUPIDO trials are two multicenter randomized controlled trials in which women with stress urinary incontinence (SUI) or occult stress urinary incontinence (OSUI) are randomized to prolapse surgery combined with anti incontinence surgery (concomitant surgery) or to prolapse surgery only. Patients with at least stage 2 POP are eligible, women with evident SUI are randomized in CUPIDO I. Patients without SUI are eligible for CUPIDO II and will have urodynamic evaluation or a standardized redression test. Women with OSUI are randomized, women without OSUI are followed up but not randomized.

The primary outcome measure is absence of SUI twelve months after surgery. Furthermore, economic evaluations are conducted, and the effectiveness of urodynamic investigation is evaluated against a non-invasive way to determine SUI in women with POP.

A total of 450 women will be included in the study.

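### The 10% loss allowance was multiplied on rather than divided out, so both randomised totals fall just short of the evaluable numbers the plan says it needs; the effect on power is about half a point

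*Protocol article*

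**What the plan says.** All of the figures stand in the Protocol article under Sample size calculation.

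- **CUPIDO I:** 57 women per arm, for 70% against 90% success, 80% power and one-sided testing at 0.05. The allowance for loss follows: "Taking into account 10% loss to follow up a total of 126 patients will be included in the study".
- **CUPIDO II:** "For the group of women with occult SUI 73 are needed in each arm", for "95% versus 80% continence respectively", "with a power of 80% and α of 0.05". The section does not say whether the test is one- or two-sided. The allowance for loss follows: "Taking into account 10% loss to follow up 160 patients will be randomized".
- **Women tested in CUPIDO II:** the plan expects "50% of these patients to have OSUI" and concludes: "We will therefore include 320 women in the study to perform urodynamic investigation".

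The Statistics section says that proportions will be compared with a chi-square test and mentions no continuity correction. Randomisation is 1:1 in both trials.

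**The concern.** A loss allowance is meant to ensure that, once the expected share of women has dropped out, the number required by the power calculation is still there. If a fraction d is lost, the number to randomise is n/(1 − d). Using n × (1 + d) gives too few, because the loss applies to the enlarged total and not to n.

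Both totals look like the second form. The plan would then state a required number of evaluable women and, in the next sentence, a randomised total that does not deliver it under the plan's own assumption. What is at stake is internal consistency and whether the 80% power claim in CUPIDO II holds as written.

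**Working it through.** **Inputs (Sample size calculation).** CUPIDO I: 57 per arm, 114 in total, 70% v 90%, one-sided 0.05, total 126. CUPIDO II: 73 per arm, 146 in total, 80% v 95%, α 0.05, total 160. Loss 10% in both.

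**1. The per-arm numbers.**
- CUPIDO II, two-sided, unpooled variance: n = (1.960 + 0.842)² × (0.95×0.05 + 0.80×0.20) / 0.15² = 72.4, so 73. This matches the plan. The pooled-variance formula gives 76.
- CUPIDO I, one-sided, pooled: 49 without continuity correction and 58 with it. The stated 57 is close to the corrected size.

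**2. The plan's totals.**
- CUPIDO II: 146 × 1.1 = 160.6; per arm 73 × 1.1 = 80.3, and 2 × 80 = 160.
- CUPIDO I: 114 × 1.1 = 125.4; per arm 57 × 1.1 = 62.7, and 2 × 63 = 126.

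Multiplying by 1.1 per arm and rounding to the nearest whole number reproduces both stated totals.

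**3. What remains after 10% loss, and what division gives.**

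| Trial | Needed | Stated total | Stated × 0.9 | Short by | Needed / 0.9 | Rounded up (equal arms) |
|---|---|---|---|---|---|---|
| CUPIDO I | 114 | 126 | 113.4 | 0.6 | 126.7 | 127 (128) |
| CUPIDO II | 146 | 160 | 144.0 | 2.0 | 162.2 | 163 (164) |

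**4. Power in CUPIDO II (80% v 95%, two-sided 0.05).**

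Unpooled: power = Φ(0.15 / √(0.2075/n) − 1.960)
- n = 73: Φ(2.814 − 1.960) = 80.3%
- n = 72: Φ(2.794 − 1.960) = 79.8%

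Pooled (mean rate 0.875), as for an uncorrected chi-square test: power = Φ((0.15 − 1.960 × √(0.21875/n)) / √(0.2075/n))
- n = 73: 78.8%
- n = 72: 78.3%

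The loss is about 0.5 point by either formula. If a one-sided test had been meant, the pooled figures would be 87.0% and 86.5%: the same half point, with 80% not at risk.

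**5. Power in CUPIDO I (70% v 90%, one-sided 0.05, pooled, uncorrected; mean rate 0.80).**

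Power = Φ((0.20 − 1.645 × √(0.32/n)) / √(0.30/n))
- n = 57: 85.5%
- n = 56.7: 85.3%

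**6. Women tested in CUPIDO II.** The plan's figure is 160 / 0.50 = 320. With the corrected totals it is 163 / 0.50 = 326, or 164 / 0.50 = 328.

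**The case against.** The strongest reply is that this is a rounding-level matter. The shortfall is 2 women in CUPIDO II and less than 1 in CUPIDO I. The stated totals deliver the needed numbers if loss is at most 14/160 = 8.75% and 12/126 = 9.5% respectively, and 10% is itself a round planning guess. No design choice, analysis or conclusion would change. This stands, and it is why the point is minor. It does not remove the inconsistency, because the plan gives the required number, the loss and the total, and the three do not fit together.

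For CUPIDO I there is a further reply, which also stands. The 57 per arm is well above the 49 of the uncorrected formula, and the Statistics section names no correction. A count is missed there, but 80% power is not.

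Two stronger readings are tempting. A reader might infer that CUPIDO II recruitment closes at 320 women tested, so that the number randomised, and with it the power, is left to chance and to the true rate of occult incontinence. The text does not say this. It fixes 160 as the number to be randomised and derives 320 from it, and nothing says that inclusion stops at 320 if fewer than 160 women qualify. Any probability of falling short would rest on a stopping rule that the article does not contain. A reader might also set the abstract's statement "A total of 450 women will be included in the study" against 126 + 320 = 446. The gap is under 1% and is best read as rounding.

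**Conclusion.** The point holds as a minor arithmetic correction. The 10% loss was allowed for by multiplying by 1.1, and under the plan's own assumption the totals leave 144 evaluable women against 146 needed in CUPIDO II, and 113.4 against 114 in CUPIDO I.

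The cost in CUPIDO II is about half a point of power, which leaves it just under the stated 80% (79.8% unpooled, 78.3% pooled). CUPIDO I stays near 85%. The CUPIDO II figures assume a two-sided test, which the article does not state but which the number 73 fits. All figures assume exactly 10% loss, split evenly between the arms, and the plan's success rates. The documents do not support a larger claim that either trial is materially underpowered by this slip, or that recruitment is capped at 320.

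**What to change.** Make one of two changes in the sample size sections.

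1. **Keep 126 and 160** and state what they give after 10% loss: about 56.7 and 72 evaluable women per arm, with power just under 80% in CUPIDO II. This costs nothing beyond the wording.
2. **Correct the totals** to 127 (128 for equal arms) in CUPIDO I and 163 (164 for equal arms) in CUPIDO II, and restate the expected number tested in CUPIDO II as about 326 to 328 at 50% occult incontinence. With equal arms this adds 2 randomised women in CUPIDO I and 4 in CUPIDO II, and about 8 more women tested.

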### Statistics

The analysis is performed according to the *intention to treat *principle. Data will be presented as numbers (percentage) for nominal variables or means (standard deviation) for interval variables. For interval variables, differences between the two groups will be analyzed with a Students t-test, proportions will be compared using the Chi-square test.

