**Figure 1 F1:**
[figure not shown]
**Flowchart CUPIDO I**.

**Table 1 T1:** Participating hospitals in the Netherlands.

Academic Medical Center, Amsterdam
Alant Vrouw, Bilthoven
Deventer Hospital, Deventer
Martini Hospital, Groningen
Maxima Medical Center, Eindhoven
Medical Center Leeuwarden, Leeuwarden
Reinier de Graaf Groep, Delft
Sint Antonius Hospital, Nieuwegein
TweeSteden Hospital, Tilburg
Twenteborg Hospital, Almelo
University Medical Center, Groningen
University Medical Center, Nijmegen
University Medical Center, Maastricht
VieCuri Medical Center, Venlo

**Table 2 T2:** Inclusion and exclusion criteria CUPIDO I.

Inclusion criteria	Exclusion criteria
≥ 18 years old	Inability to give informed consent
≥ stage 2 prolapse	(Recent or planned) pregnancy
Intended surgery for prolapse	Previous anti-incontinence surgery
	Recent prolapse surgery (<6 months)
	Previous surgery to bladder or urethra or diverticulum
	Systemic disease which could influence bladder function
	Planned chemo- or radiotherapy for neoplasm
	Participation in another study which could influence the results
	Chronic urinary retention
	Not predominant SUI (urge incontinence)
	Rectocele only

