### Randomization

Patients with SUI will be randomized through a website according to a computer-generated randomization sequence. The randomization sequence is computer generated with a block size of four. Stratified randomization is applied for centre and leading edge of the prolapse. Randomization will be 1:1 for concomitant surgery and prolapse surgery only. The data are web based registered. Women receive a case number at randomization to treat their data anonymously.

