### Outcome measurements

The outcome measures are equal for both trials. Their primary outcome is absence of urinary (stress) incontinence and subsequent treatment for urinary (stress) incontinence 12 months after surgery. Secondary outcomes are absence of SUI at 6 months after surgery, anatomical results and repeated treatment for pelvic organ prolapse, disease specific and general quality of life, morbidity and quality of life, and quality adjusted life-years at 6 and 12 months postoperatively. We will also study general satisfaction and costs.

Patients in the studies will be followed from surgery until 12 months later. Follow up will consist of various elements. At inclusion the following data will be recorded:

1. History and clinical examination

2. 48 hour voiding diary

3. Dutch validated version of the Urinary Distress Inventory, a disease specific questionnaire comprising 17 questions, to assess the presence and experienced discomfort of pelvic floor problems. The UDI consists of 5 domains: discomfort/pain, urinary incontinence, overactive bladder, genital prolapse, and obstructive micturition. The total UDI score is defined as the average of the 5 domain scores, and can be used to assess cost effectiveness by measuring quality of life [20,21].

4. Short Form 36, with 36 questions on physical, mental and social health to assess generic quality of life [22].

5. EQ-5D, a disease non-specific quality of life questionnaire, to derive health utilities and the corresponding quality adjusted life years (QALYs) This is the change in quality of life induced by the treatment multiplied by the duration of treatment effect [23,24].

6. Health and Labour Questionnaire Short Form, to measure the impact of disease and treatment on absence from work, reduced productivity, unpaid labor production, and labor- related problems [25]

7. GIS question, a global impression of the prolapse and urinary complaints

8. Stress test with a bladder volume of at least 300 millilitres. The patient is instructed to cough four or five times while lying in lithotomy position. In case of a negative stress test, the test is repeated with redression of the prolapse. This is done by repositioning the cervix or vaginal vault using a cotton swab.

9. Post-voiding residual bladder volume measured by ultrasound

10. Examination of the prolapse using POP-Q

11. Examination of pelvic floor function

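### The planned t-test and chi-square test are valid but ignore the baseline scores and the randomisation strata; precision is lost mainly in the quality-of-life and symptom scores

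*Protocol article*

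**What the plan says.** - **Tests (Statistics).** Under intention to treat, for interval variables "differences between the two groups will be analyzed with a Students t-test, proportions will be compared using the Chi-square test". No stratum, covariate or model is named there or elsewhere in the article.
- **Randomisation (the Randomization sections of CUPIDO I and CUPIDO II).** "Stratified randomization is applied for centre and leading edge of the prolapse"; "The randomization sequence is computer generated with a block size of four"; "Randomization will be 1:1 for concomitant surgery and prolapse surgery only". Table 1 lists 14 hospitals. The number of leading-edge categories is not given.
- **Baseline data (Outcome measurements).** Under "At inclusion the following data will be recorded" come the "Dutch validated version of the Urinary Distress Inventory, a disease specific questionnaire comprising 17 questions", the "Short Form 36, with 36 questions on physical, mental and social health to assess generic quality of life" and the EQ-5D. The same section has the questionnaires sent again with the visits at 6 weeks, 6 months and 12 months.
- **Primary outcome (Outcome measurements).** Binary: free of (stress) incontinence and of further treatment for it at 12 months.

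**The concern.** The design uses information that the analysis then leaves out, in two separate ways.

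*Strata.* Blocking within centre and leading edge balances those factors between arms, so differences between strata no longer add to the true error of the treatment difference. An unstratified test still counts them. If the factors are prognostic, the reported SE is somewhat too large and the test is conservative.

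*Baseline scores.* A woman's own baseline score is not a stratification factor. Leaving it out gives a correct SE, but a larger one than necessary, and any chance baseline difference between the arms stays in the estimate.

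The second matters more. The secondary aim of both trials is whether concomitant surgery increases adverse effects such as obstructive voiding symptoms and detrusor overactivity. The UDI has domains for obstructive micturition and overactive bladder, and neither trial is sized on them. Wider intervals there make a real harm easier to miss.

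**Working it through.** **1. The plan's own figures, which are unstratified two-proportion calculations**

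- CUPIDO I: 70% v 90%, one-sided 0.05, power 80%. Pooled formula: n = [1.645·√(2·0.8·0.2) + 0.842·√(0.7·0.3 + 0.9·0.1)]² / 0.2² = 48.4. With continuity correction: (48.4/4)·[1 + √(1 + 4/(48.4·0.2))]² = 58.0. The plan states 57.
- CUPIDO II: 80% v 95%, two-sided 0.05, power 80%. Unpooled formula: n = (1.960 + 0.842)²·(0.95·0.05 + 0.80·0.20) / 0.15² = 72.4, so 73, as stated.
- Exact power of the uncorrected chi-square: CUPIDO I with 57 per arm, 86% one-sided as planned (79% if two-sided); CUPIDO II with 73 per arm, 82% two-sided.

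**2. Interval outcomes: cost of ignoring the baseline score**

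The documents give no correlation ρ between baseline and follow-up, so 0.3-0.6 is assumed. The ANCOVA error variance is (1 − ρ²) times that of the t-test on follow-up scores. The t-test SE is therefore 1/√(1 − ρ²) times larger, and the equivalent sample-size ratio is 1/(1 − ρ²).

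| ρ | 1 − ρ² | t-test SE larger by | equivalent extra patients |
|---|---|---|---|
| 0.3 | 0.91 | 4.8% | 10% |
| 0.5 | 0.75 | 15.5% | 33% |
| 0.6 | 0.64 | 25.0% | 56% |

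Simulation with 114 women, blocks of four and 14 strata gave ANCOVA/t-test SE ratios of about 0.96, 0.87 and 0.80, in agreement.

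The article does not say whether the t-test uses follow-up or change scores. For change scores with equal variances, the SE relative to ANCOVA is √[2(1 − ρ)/(1 − ρ²)] = √[2/(1 + ρ)], which is 1.24, 1.15 and 1.12 for ρ = 0.3, 0.5 and 0.6. ANCOVA is more precise either way.

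**3. Cost of ignoring the strata**

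Stratum effects are not in the documents. Simulated with permuted blocks of four, the plan's rates and 57 or 73 women per arm:

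| Between-stratum SD (logit) | reported/true SE, CUPIDO I | reported/true SE, CUPIDO II |
|---|---|---|
| 0 | 1.00 | 1.00-1.02 |
| 0.5 | 1.01-1.02 | 1.00 |
| 1.0 | 1.05 | 1.02-1.03 |

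The 1.02 at SD 0 should be 1, so deviations of that size are close to simulation noise. With SD 1.0 the chi-square type I error falls to about 0.037-0.046 against 0.05. For interval outcomes, the t-test SE is about 5-6% too large if strata explain 10% of the variance.

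**4. What stratifying the primary test does to power (chi-square → Cochran-Mantel-Haenszel)**

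| | SD 0 | SD 0.5 | SD 1.0 |
|---|---|---|---|
| CUPIDO I, 14 strata | 86.3 → 85.8% | 87.0 → 86.9% | 87.6 → 89.5% |
| CUPIDO I, 42 strata | 86.1 → 79.8% | 86.4 → 81.6% | 86.7 → 84.7% |
| CUPIDO II, 14 strata | 83.0 → 82.4% | 81.2 → 81.0% | 83.2 → 84.9% |
| CUPIDO II, 42 strata | 82.4 → 77.5% | 81.6 → 77.5% | 83.5 → 81.6% |

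The 42 strata assume three leading-edge levels in each of 14 centres. That leaves 114/42 = 2.7 women per cell in CUPIDO I and 146/42 = 3.5 in CUPIDO II, fewer than one block. A further simulation with 114 evaluable women gave about -1 to +2 points for stratifying by leading edge or by pooled centre. Full cross-stratification lost up to 6-9 points with no stratum effects and 3-5 with moderate ones.

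**The case against.** The strongest case against is that nothing is invalid. Both tests keep type I error at or below nominal, the primary outcome barely gains, and a badly chosen stratified test would lose power. The correlations and stratum effects are assumed, and a condensed article may leave covariates to an analysis plan that is not shown.

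Most of that stands, and it limits the point to efficiency. It does not remove it: the article goes beyond silence by naming the tests, and ANCOVA gains precision at every correlation in the assumed range.

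A reader might infer more than the documents support:

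- *That the trials are underpowered because of this choice.* They are not. Under the plan's own rates and sample sizes the plain chi-square has 86% power in CUPIDO I, tested one-sided as planned, and 82% in CUPIDO II. Only a two-sided CUPIDO I test, which the sample-size section does not plan, falls just below 80%.
- *That omitting baseline scores overstates the SE.* It enlarges a correct SE. Overstatement comes only through the strata, and only if they are prognostic.
- *That the test must stratify on every randomisation cell.* The 42-stratum results show that this would usually do harm.

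**Conclusion.** The point holds as a modest matter of efficiency. The planned tests are valid and at worst slightly conservative. The worthwhile gain is in the UDI, SF-36 and EQ-5D comparisons, where unadjusted SEs are about 5-25% larger than ANCOVA. This rests on the assumed baseline correlation of 0.3-0.6. For the primary outcome the reported SE is at most about 5% too large, and a sensible stratified test changes power by about -1 to +2 points. Those figures rest on assumed stratum effects of up to SD 1.0 on the logit scale. The size of the loss from full cross-stratification also depends on the assumed three leading-edge levels.

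**What to change.** Amend Statistics, before outcome data are examined, as follows:

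- **UDI domains, SF-36, EQ-5D:** ANCOVA on the follow-up score, with baseline score and leading edge as covariates and centre as a random or pooled effect.
- **Binary primary outcome:** Mantel-Haenszel test and risk difference with 95% CI, stratified either by leading edge or by centre with small centres pooled. Choose one and write down the pooling rule in advance. Do not use the full centre-by-edge cross-classification.
- **Sensitivity analyses:** keep the crude t-test and chi-square test.

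The cost is a sentence or two of text and a few lines of code. Every variable needed is already collected, and the sample sizes need not change.

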### Time plan

Inclusion for the Cupido study began in November 2007. The inclusion is planned to be finished in July 2010 for Cupido 1 and in March 2011 for Cupido 2. Patients are followed up to 12 months after surgery, so this will take until July 2011 and March 2012 for Cupido 1 and 2 respectively. The study is conducted in several Dutch centers assembled in the urogynaecology consortium. This consortium consists of Dutch centers cooperating in multicenter trials.

